##### Intervention Acceptability

Acceptability of the intervention will be assessed using semi-structured interviews with intervention participants. Data will be analyzed using thematic analysis as well as deductive charting using the APEASE (Acceptability, Practicality, Effectiveness, Affordability, Side effects, Equity) criteria (44).

##### Productivity

Work productivity will be assessed using measures of absenteeism, presenteeism, and ecological momentary assessment (EMA) at baseline and during week eight of the study. Absenteeism will be measured using self-report at baseline and at the end of the eighth week. Three questions to assess unsanctioned absences will be used from a previous study (45). This includes the number of days off work in the last 2 weeks for sickness (colds, flu, etc.), the number of days off work for mental health reasons (stress, burnout, etc.), and the number of days excused work (e.g., compassionate leave, educational leave, parental leave). Self-reported absenteeism will be calculated by summing the number of days reported across all three questions. Presenteeism will be measured using the 8-item Work Limitations Questionnaire (WLQ), which is a short version of the original 25-item WLQ (46). This version of the WLQ is a reliable and valid alternative to the longer questionnaire (47). The WLQ requires participants to self-report their level of difficulty (or ability) to perform eight specific job demands in the last 2 weeks, with answers grouped into four work limitation scales on time management, physical, mental, and output demands.

The final measure of productivity is EMA, which has been used previously in a variety of different contexts to measure physical activity and sedentary behavior (48–50). Prompt software will be installed on participant's smartphones to deliver the EMA. Prompts to complete the EMA will occur at random, four times each week day between 9 am to 5 pm (51). In total, participants will be requested to respond to and complete a maximum of 12 EMA surveys in a week. Once a participant has completed 12 surveys, the prompt software will no longer prompt that participant to respond (51). The questionnaire includes items about posture, musculoskeletal issues, task being performed, social interactions, mood, and perception of engagement and productivity (Table 5), typically taking <1 min to complete each time.

**Table 5 T5:** Ecological momentary assessment productivity questions.

**Survey question**	**Responses**
What posture are you in?	Sitting/Standing/Walking
Are you experiencing musculoskeletal pain right now?	Yes/No
What are you currently doing?	In a meeting/Working at my desk/Working away from my desk/Eating/In transit/On a break/Other
How many people are you doing this with?	Alone / With 1 other person/ With 2–5 people/With 6+ people
On a scale of 1 to 10, 1 being not at all and 10 being extremely, please rate your emotions at this moment	
Happy	
Stressed	
Energized	
Anxious	
Productive	
Motivated	
Engaged	
Creative	

##### Cardiometabolic Risk Biomarkers

All cardiometabolic risk biomarker measures will be taken at baseline and within 5 days post-intervention. This includes the following:

###### Fasting Blood Glucose and Lipid Profile.

Blood samples taken after an overnight fast of at least 10 h using a finger prick method with a lancet (52). Blood samples will be analyzed with a Cholestech LDX analyzer (Cholestech Corp., Hayward, CA., USA) to provide measures of total cholesterol, high-density lipoprotein cholesterol, low-density lipoprotein cholesterol, triglycerides and blood glucose (52).

*Blood Pressure*. Resting systolic and diastolic blood pressure will be measured on the right arm after resting for at least 10 min in a seated position using an automated blood pressure monitor (Omron HEM705 CP, Omron Healthcare UK Limited, Milton Keynes, UK) validated by the European Society of Hypertension (53). The average of two blood pressure readings with a 2-min rest between each will be used for analysis.

*Anthropometry*. The standardized procedure of Lohman et al., (54) will be used. Height is measured with a stadiometer (Horltain Ltd., Crymych, UK) to the nearest 0.1 cm, while mass is measured with an electronic weighing scale (Tanita Corp., Tokyo, Japan) to the nearest 0.1 kg. Waist circumference is recorded to the nearest 0.1 cm measured around the waist at navel-level while participants are standing (55, 56). All measures will be taken by the same investigator to avoid inter-investigator variability. Body mass index will be calculated as: weight / height^2^.

##### Psychological and Mental Wellbeing

Perceived levels of stress will be measured using the Cohen Perceived Stress Scale (57), which evaluates the unpredictability, uncontrollability and overload of an individual's life, and has high validity and reliability (57). The questionnaire requires participants to rank the frequency of feelings and thoughts using a five-point Likert scale ranging from 1 “*Never*” to 5 “*Very often”*. Participant's mood states will be measured using the Positive and Negative Affect Schedule (PANAS), which is a 20-item self-report measure of positive affect and negative affect (58). The questionnaire makes use of words that describe feelings and emotions on a scale from 1 “*Very slightly or Not at all”* to 5 “*Extremely*.” The PANAS positive and negative affect scales have high reliability (59). Changes in participants' mental wellbeing will be assessed using the Warwick-Edinburgh Mental Well-Being Scale (WEMWBS) (60), which is a 14-item scale that explores feelings and thoughts over the last 2 weeks. This study was registered to obtain permission to use WEMWBS (ID: 448654978) on warwick.ac.uk. The WEMWBS classifies individuals as having low, average or high mental wellbeing and can measure changes over time. The questionnaire asks questions such as “I have been feeling confident” and participants will need to rate themselves on a scale from 1 “*None of the time”* to 5 “*All of the time.”* It has been reported to have high test-retest reliability (61).

### Statistical Analysis

All statistical analyses will be performed using SPSS (IBM Corp, Armonk, New York, USA). Data will be assessed for normality using the Shapiro-Wilk test owing to the relatively small sample size. Linear mixed models will be used with arm and time as fixed effects, participant ID and cluster ID as random effects, and the baseline value of each variable as a covariate. An additional linear mixed model will be used to compare the effect of standing vs. sitting posture for the EMA variables at follow-up with posture and arm as fixed effects, participant ID and cluster ID as random effects, and the baseline value of each variable as a covariate. The Sidak *post-hoc* adjustment will be used to adjust for multiple comparisons in all models. Adjustments for missing data will be made using the estimated marginal means procedure of the linear mixed models. If there was a large number of non-normally distributed variables, the bias-corrected and accelerated (BCa) bootstrap method will be used to produce unbiased estimates of the confidence limits for all data (62). Data will be presented as mean and 95% confidence intervals of the bootstrapping procedure. The level of statistical significance will be *p* ≤ 0.05 for two-tailed tests. Magnitude of effects will be reported as Hedges' *g*, which is a corrected effect size based on Cohen's *d* that is suitable for use in small sample sizes of 20 or less per group to produce an unbiased estimate of the population effect size (63). The magnitude of the effect sizes will be considered to be small if they are ≥ 0.2, moderate if ≥ 0.6, and large if ≥ 1.2, using the scale proposed by Hopkins et al. (64). Adherence to the intervention will be assessed using the Wilcoxon signed rank test to compare baseline and follow-up classifications. The standardized test statistic of the Wilcoxon test will be converted to an effect statistic by dividing it by the square root of N (65), which can then be interpreted as *r* using the scales of Cohen (66) and Hopkins et al. (64).

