### Measurements

All measures for both intervention and control groups will be performed at baseline and during the final week of the 8-week study period. Questionnaires will be completed online using Qualtrics survey software (Qualtrics, Provo, Utah, USA) with physical measures taking place at participant's workplaces in a private room.

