#### Primary Outcome Measure: Workplace Sitting Time

The primary outcome measure is sitting time at work, which will be measured using an activPAL3 activity monitor (PAL Technologies Ltd., Glasgow, UK). The activPAL is a portable lightweight device, which is usually worn on the front of the mid-thigh to take measurement of postural information by recognizing periods of lying down/sitting, standing, and stepping based on the inclination of the thigh (39, 40). The activPAL has high reliability and validity for assessing sitting, standing and stepping (41). In this study, the device will be worn on the right thigh for seven full consecutive days (42) at baseline and during the last week of the intervention. The device will be waterproofed by wrapping it within a nitrile sleeve and an adhesive medical dressing. In addition, participants will complete a diary to keep record of their waking time, working hours and time they go to bed while wearing the device to enable calculation of waking and working time wear periods (42). Data from the activPAL will be considered valid only if the device is worn for a minimum of 75% of the workplace monitoring time (39, 40). The sitting time at work variable will be normalized by expressing it as a percentage of the duration of the working day for each participant.

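### The main mixed model uses baseline as both outcome and covariate: as written the arm coefficient is half the week-8 effect, and with an arm-by-time term its standard error is too small

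*Protocol article*

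**What the plan says.** Three statements in the protocol article bear on this.

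- **Model** (Statistical Analysis): the fixed effects, random effects and covariate are given as "with arm and time as fixed effects, participant ID and cluster ID as random effects, and the baseline value of each variable as a covariate". No arm-by-time term is listed, and no coefficient or contrast is named as the intervention effect.
- **Schedule** (Measurements): "All measures for both intervention and control groups will be performed at baseline and during the final week of the 8-week study period". The primary outcome follows it: "the device will be worn on the right thigh for seven full consecutive days (42) at baseline and during the last week of the intervention".
- **Missing data** (Statistical Analysis): "Adjustments for missing data will be made using the estimated marginal means procedure of the linear mixed models".

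Two neighbouring sentences matter for the reading. A Sidak "post-hoc* adjustment will be used to adjust for multiple comparisons in all models" is planned. A separate EMA model is to "compare the effect of standing vs. sitting posture for the EMA variables at follow-up with posture and arm as fixed effects"; it has no time term.

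**The concern.** With one follow-up occasion, the model can be read in three ways, and none works.

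1. **Baseline rows in the outcome, main effects only (as written).** The arm coefficient averages the arm difference over both occasions. Once the baseline value is conditioned on, the difference at baseline is zero by construction, so the week-8 effect is diluted.
2. **Baseline rows in the outcome, arm-by-time added.** The point estimate is right. But each baseline row is still partly predicted by itself, which shrinks the pooled residual variance and hence the standard error.
3. **Baseline as covariate only.** Time then has one level and cannot be estimated. For outcomes with a single week-8 value, the participant intercept cannot be separated from the residual.

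At stake are the estimate and confidence interval for workplace sitting time and for every other continuous outcome analysed by this model. The missing-data sentence does not repair this. Marginal means are predictions from the fitted model and do not themselves adjust for missing values. Under readings 1 and 2, a participant without week-8 data contributes only a row in which outcome equals covariate.

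**Working it through.** The article gives no effect size, power or standard error for this model, so there is no figure of its own to reproduce.

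**Inputs from the article.** Two occasions (Measurements); 18 per group and 20% attrition (Sample Size); about eight offices averaging six people (Randomization).

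**Assumptions.** Baseline to week-8 correlation r of 0.3 to 0.7 and, for coverage, a true effect of 0.8 SD. SD is set to 1, and clustering is ignored except in the REML check in step 1.

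**Step 1: size of the arm coefficient as written.** With two rows per participant and no interaction, the arm coefficient comes from regressing (y0 + y1)/2 on arm and y0. Given y0, the y0 half carries no arm difference. Therefore

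arm coefficient = (0 + week-8 adjusted effect)/2.

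This is exact for complete data and does not depend on r, SD or ICC. If a fraction f of participants have week-8 data, the week-8 rows carry weight f/(1 + f) when the participant variance is estimated at zero. That happens here because the two residuals of a participant are negatively correlated. With f = 0.8, the weight is 0.8/1.8 = 0.444.

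REML fits with office and participant effects (8 offices of 6, true effect -10, SD 12, ICC 0.05, r from 0.4 to 0.8) agree:

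| Quantity | Complete data | 20% missing |
|---|---|---|
| Arm coefficient as written | -5.03 to -5.09 | -4.42 to -4.47 |
| Median ratio to week-8 ANCOVA | 0.500 | 0.443 |
| Arm-by-time term, if added | -9.96 to -9.98 | -9.94 to -9.95 |
| Week-8 ANCOVA | -10.07 to -10.17 | -10.05 to -10.23 |

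**Step 2: coverage as written.** With 18 per arm and a true effect of 0.8 SD, the mean arm coefficient is 0.40, against 0.80 for week-8 ANCOVA. The 95% interval contains 0.8 in about 44%, 32% and 16% of trials at r = 0.3, 0.5 and 0.7.

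**Step 3: type I error of the arm test as written.** The baseline slope is 1 in baseline rows and r in week-8 rows, so the pooled slope is (1 + r)/2. The pooled residual variance is

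s² = (1 - r)²/4 + (1 - r²)/2.

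At r = 0.5, s² = 0.0625 + 0.375 = 0.4375. The true variance of the arm coefficient under no effect is (1 - r²)/(2n) = 0.375/n, and the model reports s²/n = 0.4375/n. The test is slightly conservative, at about 3%.

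**Step 4: arm-by-time added, baseline covariate kept (r = 0.5, complete data).**

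- Interaction: true variance 4(1 - r)/n = 2.00/n; reported 4s²/n = 1.75/n. SD ratio √(2.00/1.75) = 1.069. Type I error = P(|Z| > 1.96/1.069) = 6.7%.
- Week-8 contrast: true variance 2[(1 - r²) + (1 - r)²/4]/n = 1.625/n; reported 2s²/n = 0.875/n. SD ratio √(1.625/0.875) = 1.363. Type I error = P(|Z| > 1.96/1.363) = 15.0%.

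The same formulas give 7.5% and 14.3% at r = 0.3, and 5.9% and 15.7% at r = 0.7. Simulation agrees: about 6-8% and 14-16%.

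**The case against.** The strongest reply is that the article lists factors and does not say main effects only. A Sidak adjustment has nothing to adjust for two-level main effects, so it points to arm-by-time cell comparisons, and a condensed article may simply have dropped the interaction. This stands in part: the halving is conditional on the model being fitted as written. It does not rescue the model, because baseline would still be response and covariate, and step 4 shows the error bars would be wrong.

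A reader might infer more than the article supports:

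- **That the efficacy test is invalid as written.** It is not. Type I error is about 3%, and one simulation at 0.8 SD gave power of 0.69 against 0.74 for ANCOVA. The damage is to the estimate and interval.
- **That every outcome is affected.** The EMA posture model uses follow-up only, adherence uses a Wilcoxon test, feasibility uses rates and acceptability uses interviews.
- **That the participant effect can never be estimated without baseline rows.** EMA has up to 12 surveys a week, so there it can be.
- **That Hedges' g is halved and a full trial would be four times too large.** The article does not say that g comes from the arm coefficient, and the Sample Size section gives estimating the standard deviation as the pilot's main purpose.
- **That the 45 to 83 min reductions in the Introduction would appear as half.** Those come from other interventions at 12 months; the primary outcome here is a percentage of the working day.
- **That missing data get no handling at all.** A likelihood-based mixed model does use the available rows. The fault is in crediting the marginal means with the adjustment.

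**Conclusion.** The point holds. The main model contradicts the two-occasion schedule, and every reading of it gives a wrong estimate, a wrong standard error or a term that cannot be fitted.

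- **As written:** the arm coefficient is 0.50 of the week-8 adjusted effect with complete data, whatever the correlation, SD or ICC, and about 0.44 with 20% missing week-8 data. Coverage of about 16% to 44% rests on 18 per arm, a true effect of 0.8 SD and r of 0.7 to 0.3, all without clustering.
- **With an unwritten arm-by-time term:** the estimate is unbiased, with type I error of about 6-8% for the interaction and 14-16% for the week-8 contrast (complete data, r of 0.3 to 0.7, no clustering).

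The scope is the primary outcome and the other continuous outcomes analysed by the main model. The article does not establish which contrast will be reported, so it cannot be said that the published effect will be halved. It can be said that the stated rule needs correcting before the data are analysed.

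**What to change.** Replace the main-model sentence with one of the following.

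1. **Week-8 model.** For single-value outcomes, take the week-8 value as the outcome, with arm and the baseline value as fixed effects and a random intercept for office. Drop time and the participant random effect, but keep the participant effect for the repeated EMA surveys. Name the arm coefficient as the intervention effect.
2. **Two-occasion model.** Keep baseline and week 8 as outcomes, with an arm-by-time term, arms constrained equal at baseline and no baseline covariate. Name the week-8 arm contrast as the effect. This keeps participants without week-8 data under a missing-at-random assumption, and a statement of that assumption should replace the sentence on estimated marginal means.

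Either change is analysis wording only. It needs no new data and no change to the schedule or the sample size.

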There is a growing body of evidence that suggests height-adjustable workstations (i.e., a workstation that permits the user to interchangeably work in a seated or standing posture) could be effective for decreasing sitting in the workplace (13). When height-adjustable workstations are provided as part of multi-component interventions that also include strategies such as education, manager support, standing meetings, self-monitoring and social support, workplace sitting has been significantly reduced by 45 to 83 min/work shift after 12 months (14, 15). Although these interventions appear promising, management of organizations might be reluctant to implement them if productivity is negatively affected (16). With respect to productivity concerns, a systematic review reported that productivity is likely to be unaffected by using a height-adjustable workstation (17). There are also limited studies that have reported taking employee's perceptions and experiences into account when developing interventions to reduce workplace sitting (18), which may limit intervention adherence and effectiveness. By involving the target audience in the development of interventions, this will help to ensure their needs are met and enhance their adherence and engagement (19). The Behavior Change Wheel (BCW) (20, 21) has been recommended for guiding the systematic process of developing an intervention using a framework that takes into account the needs of the target audience. To the author's knowledge, only one previous office workplace intervention has been developed using the BCW (18); the SMArT Work intervention in National Health Service employees led to significant reductions in sitting at work and improvements in job performance, work engagement, occupational fatigue, sickness presenteeism, anxiety and quality of life over 12 months (15). Further research is required in other occupational groups to strengthen the evidence base for incorporating a focus on reducing and breaking up sitting in workplace policy and practice. Demonstrating the effectiveness of such interventions for improving work-related outcomes, such as worker productivity, will be important for encouraging the adoption of such changes in policy and practice. The use of ecological momentary assessment (EMA) facilitated through smartphone technology provides the opportunity to collect simultaneous time-stamped data with limited recall bias to elucidate on the temporal effects of posture and activities on work performance throughout the workday (22, 23). However, the effects of workplace sitting interventions on EMA measures of work-related outcomes is limited.

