## Discussion

This pilot cluster-randomized controlled trial will evaluate the efficacy of a tailored workplace intervention for reducing and breaking up sitting, productivity, wellbeing and cardiometabolic risk biomarkers. The multi-component intervention protocol was designed using a participatory approach informed by the BCW and identification of intervention functions, policy categories and BCTs using the APEASE criteria to enhance the intervention's adherence and effectiveness. In addition to employing this systematic and evidence-based process for developing the intervention, further strengths of this study include the cluster-randomized design to minimize contamination between groups that are located within the same organization. The study will also be conducted within an ecologically valid office environment, thus enhancing its real-world application. Ecological momentary assessment will be used to assess temporal effects of the intervention on productivity during specific postures and work activities; this may provide important evidence to encourage changes in workplace policy and practice. Potential limitations include sample representativeness of the general office worker population as the study is being conducted only within two organizations. It will also not be possible to determine the effects of each individual strategy used as part of the intervention, which could help in determining their suitability for inclusion in occupational health promotion programmes. Furthermore, physical activity levels prior to taking blood samples will not be standardized. This may be a limitation as there is the potential for carryover effects of prior exercise on glucose and lipid levels.

In conclusion, this study will provide important evidence regarding the efficacy of a systematically developed tailored workplace intervention. This will include evaluating the effects of the intervention on a range of health and work-related outcomes, including an ecological momentary assessment of productivity that has been seldom employed in office workplace studies; this may be key in promoting the adoption and implementation of such interventions in workplace practice and policies. The findings of this study can be used to inform a future fully powered RCT to determine the effectiveness of this multi-component intervention for reducing sitting and improving health in office workers.

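### The Discussion promises the intervention's effect on productivity within specific postures, but the EMA posture model lists no posture-by-arm term, so that effect is not estimated

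*Protocol article*

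**What the plan says.** Three places in the protocol article bear on this.

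- **Discussion.** The aim is worded as an intervention effect within posture: "Ecological momentary assessment will be used to assess temporal effects of the intervention on productivity during specific postures and work activities".
- **Introduction.** The rationale for EMA is worded as an effect of posture itself; EMA can "elucidate on the temporal effects of posture and activities on work performance throughout the workday".
- **Statistical Analysis.** The general models are described as follows: "Linear mixed models will be used with arm and time as fixed effects". They contain no posture term. For EMA, a further mixed model will "compare the effect of standing vs. sitting posture for the EMA variables at follow-up with posture and arm as fixed effects", and its terms are listed in full: "with posture and arm as fixed effects, participant ID and cluster ID as random effects, and the baseline value of each variable as a covariate". No posture-by-arm term or posture-stratified arm contrast is mentioned.

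**The concern.** An intervention effect during a given posture is an arm difference among surveys answered while sitting, and another among surveys answered while standing. A model with posture and arm as separate terms does not contain these two quantities. It contains one arm difference, assumed equal in both postures, and one standing-versus-sitting difference, assumed equal in both arms.

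The intervention works largely by changing posture, through a sit-stand desk and prompts. Whether its effect on self-rated productivity depends on posture is therefore the question the Discussion sentence raises. The Introduction notes that employers may hold back if output suffers, and the Discussion presents the posture-specific EMA result as possible evidence for them. If that result is reported, it should come from a model that can produce it.

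**Working it through.** The plan gives no figure for this point, so there is none to reproduce. The check is algebra on the listed terms, followed by an illustration.

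**1. Algebra.** The listed fixed part is E[y] = b0 + b1·arm + b2·posture + b3·baseline.

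- Arm difference while sitting: b1. While standing: b1. They are equal by construction.
- Standing minus sitting in controls: b2. In the intervention arm: b2. They are also equal by construction.

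With b4·arm·posture added, the arm difference is b1 while sitting and b1 + b4 while standing. Only then are the two quantities separate.

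**2. What the additive coefficients become if the effect differs by posture.** Let τ0 and τ1 be the true arm effects while sitting and standing, Δ = τ1 − τ0, and δ the standing-minus-sitting difference in controls. Let pT and pC be the share of surveys answered standing in the intervention and control arms. With equal survey numbers per arm, and leaving the baseline covariate aside:

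- w = pT(1 − pT) / [pT(1 − pT) + pC(1 − pC)]
- posture coefficient = δ + wΔ
- arm coefficient = τ0 + Δ[pT − w(pT − pC)] = τ0 + λΔ, where λ = (1 − w)pT + w·pC

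Both depend on the posture mix.

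**3. Numbers.** From the article: two groups of 18 (Sample Size), about eight offices (Randomization), at most 12 surveys per person in a week (Productivity). Assumed, because the article gives none: δ = 0.2, the arm effects, the standing shares, and SDs of 1.0 between participants, 0.3 between offices and 1.3 within participants, on the 1–10 scale.

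- Shares 30% and 30%: w = 0.21/0.42 = 0.50; λ = 0.30.
- Shares 40% (intervention) and 10% (control): w = 0.24/0.33 = 0.727; λ = 0.273 × 0.4 + 0.727 × 0.1 = 0.182.

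The formula was set against 400 simulated trials per row, estimated by generalised least squares with the variance components known and without a baseline covariate:

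| Shares standing (int./control) | True sit / stand | Additive arm: formula / simulated | Additive posture: formula / simulated | Interaction model: sit / stand | Interaction SE |
|---|---|---|---|---|---|
| 30% / 30% | 0 / +1 | 0.30 / 0.32 | 0.70 / 0.70 | 0.01 / 1.03 | 0.28 |
| 30% / 30% | −0.5 / +0.5 | −0.20 / −0.20 | 0.70 / 0.70 | −0.50 / 0.51 | 0.28 |
| 40% / 10% | 0 / +1 | 0.18 / 0.16 | 0.93 / 0.94 | −0.02 / 0.96 | 0.36 |
| 40% / 10% | −0.5 / +0.5 | −0.32 / −0.32 | 0.93 / 0.92 | −0.50 / 0.50 | 0.36 |

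The per-trial SE of the arm coefficient is about √[2 × (0.09/4 + 1/18 + 1.69/216)] = 0.41, so the Monte Carlo error is about 0.41/√400 = 0.02. Formula and simulation agree within it.

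The true standing-versus-sitting difference is 0.2 in controls and 0.2 + 1 = 1.2 in the intervention arm. The additive posture coefficient of 0.70 to 0.94 describes neither arm.

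**4. Precision of the alternative.** Controls give at most 18 × 12 = 216 surveys in the follow-up week: about 22 standing at 10%, about 65 at 30%. The interaction's 95% half-width is 1.96 × 0.28 = 0.55 to 1.96 × 0.36 = 0.71 points, before any non-response.

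**The case against.** The case on the other side has several parts, and much of it stands.

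- **An interaction may be intended.** The article lists fixed effects and does not say main effects only. It also states: "The Sidak *post-hoc* adjustment will be used to adjust for multiple comparisons in all models". For one two-level factor the Sidak level is 1 − 0.95 = 0.05, so the adjustment does nothing unless further means are compared. That is compatible with cell comparisons, but it is a general sentence and no such term is written. A fuller plan may contain one. What can be judged is the list given here, which is otherwise complete down to random effects and covariate.
- **The model serves its own stated purpose.** This is correct. Standing versus sitting is what Statistical Analysis asks of it, and that is close to the Introduction's rationale. The conflict is with one sentence in the Discussion.
- **Posture is not randomised.** This is also correct. People choose posture after allocation, and controls have no sit-stand desk, so their few standing surveys may come from different tasks. Even with the interaction, the within-posture arm contrasts are not clean randomised comparisons. An additive posture term has the same weakness, so this does not favour the listed model.

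A reader might go further and infer that the trial cannot tell whether productivity suffers, or that real effects will be averaged away to nothing. The documents do not support either. The general arm and time model addresses the overall intervention effect, which is the employers' concern in the Introduction. Nothing says the arm coefficient of the additional model will be presented as the effect in each posture. The size of any blending rests wholly on assumed inputs. Even standing shares cannot be read from the article: its figure of 79% of the working day spent sitting leaves walking mixed with standing, and the 2 to 4 h target counts stepping as well.

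**Conclusion.** The mismatch holds. As listed, the additional EMA model estimates a standing-versus-sitting difference averaged over arms and one common arm effect. It does not estimate the intervention's effect during specific postures, and no other listed model does. This follows from the listed terms and needs no numerical assumption.

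If effects differ by posture, the arm and posture coefficients are both mix-dependent averages. How far they lie from the posture-specific values cannot be known from the documents, and the simulated values are illustrative only. If effects do not differ by posture, the additive model loses nothing. The conclusion assumes that the list of fixed effects is complete as printed.

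Severity is minor: a secondary outcome in a pilot, with the conflicting aim stated once.

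**What to change.** Either of two changes reconciles the sections.

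1. **Preferred.** Add the posture-by-arm interaction to the additional EMA model. Report the arm difference with its 95% CI while sitting and while standing, and the standing-versus-sitting difference in each arm. Label all of these exploratory, and say why: posture is chosen after randomisation, and controls without sit-stand desks will give few standing surveys, possibly during different tasks. Reporting the number of surveys per arm and posture would let readers judge this.
2. **If the interaction is not fitted.** Narrow the Discussion sentence to the standing-versus-sitting comparison that the model makes.

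The first costs one model term and one table, on data already to be collected. Its drawback is wide intervals in the standing stratum. The second costs one edited sentence. If the interaction was always intended, one clause in Statistical Analysis settles it.
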